## Flow Chart

[figure not shown]

# 1 RATIONALE

## 1.1 Medical Background

T2DM is a major burden on public health due to its high prevalence and the association with severe co-morbidities. Good glycaemic control decreases long-term morbidity and mortality. However, HbA1c levels are unsatisfactorily high for many patients. A certain number of prospective trials demonstrated that bariatric procedures (mostly RYGB) can address this problem.

So far, standard RYGB is the operation of choice for most surgeons in metabolic surgery.

However, standardised evidence based limb length recommendations do not exist for the RYGB in bariatric or metabolic surgery.

Due to a longer biliopancreatic limb, the mini-bypass might be better for both weight loss and T2DM improvement, though randomized trials are lacking.

Mimicking this effect, it may be simplest merely to exchange the limb lengths, favouring a long biliopancreatic and short alimentary limb.

Here with a Roux-en-Y reconstruction we do not have the risk of bile reflux into the pouch (and unclear GERD and cancer risk) that are seen with the mini-bypass.

The MetaSurg Study is an open, randomized controlled trial comparing standard RYGB with RYGB with changed limb length and a control arm with standard medical treatment in T2DM patients in a BMI range of 27 to 60 kg/m^2. The primary endpoint is HbA1c improvement after 1 year. The key secondary endpoint for the surgical arms is the diabetes remission rate after 1 year. Diabetes remission is defined as follows: HbA1c <6.5% without any anti-diabetic medication. 68 patients per intervention arm are planned plus 24 patients for the control arm (to be analysed: 60:60:20).

Patients will have a study follow-up of 1 year and further secondary endpoints are weight loss, visceral fat mass, therapy costs and need of medication for other co-morbidities. At our centre, there will be a lifelong follow up with continued data collection.

We expect RYGB with changed limb length to be superior to the standard RYGB with lowest HbA1c levels, a higher diabetes remission rate, relevant weight loss, and higher remission rate of obesity related co-morbidities.

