### 2.2 Secondary Objectives

Main secondary efficacy endpoint:

- T2DM remission rate after 1 year  
Definition T2DM remission: HbA1c <6.5% without indication for anti-diabetic medication
- Weight loss
- General wellbeing (SF-36 questionnaire, IPAQ) and cognitive function (TMT and MST task)
- Anthropometry (Body weight, BMI, WHR (waist to hip ratio), Body fat mass (BIA))
- Clinical parameters (fasting glucose, fasting insulin, fasting c-peptide, HOMA-IR index, Serum lipids)

Further investigated parameters:

- MRI (liver, subcutaneous and visceral fat mass, brain and spinal cord: inflammation, size general and –grey matter)
- Intima-media-thickness (IMT) A. carotis com.
- Liver volume (MRI), function and morphology
- LiMAx test (functional liver test)
- Indirect calorimetry
- Serum concentration of bile acids, GLP1, PYY, GIP, ghrelin (total and active), obestatin, leptin, leptin BP, adiponectin, chemerin, fetuin-A, Nampt, RBP4, Vaspin, OBBP, betatrophin (presently favored to be examined; extra serum will be frozen and stored for potentially new future parameters)
- Inflammatory markers: CrP, WBC, IL-6, TNF $\alpha$
- Average caloric intake per day

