## 4 TRIAL SUBJECTS

### 4.1 Inclusion Criteria

- BMI  $\geq 27$  to  $\leq 60$  kg/m^2
- T2DM
  - for patients BMI  $\geq 35$  kg/m^2: any T2DM
  - for patients BMI  $< 35$  kg/m^2:
    - unsatisfactory medical non-insulin treatment (multiple medications, HbA1c  $> 6.5\%$ , hypo- or hyperglycaemias) or
    - planned insulin treatment or ongoing insulin treatment
- males and females, age  $\geq 18$  years
- written informed consent

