1. BMI
  - a.  $\geq 27$  to  $< 50$  kg/m^2
  - b.  $\geq 50$  to  $\leq 60$  kg/m^2
2. Current insulin treatment
  - a. yes
  - b. no
3. Sex
  - a. male
  - b. female

The randomization will be performed centrally by the IFB Data Center and will be computer-assisted, using Pocock's minimization algorithm (1). Before start of recruitment, simulations will be performed to demonstrate that the randomisation procedure given the stratification parameters above yields balanced results. A randomisation ratio of 1:1 will be used.

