### 9.5.2 Planned Methods for Analysis

Efficacy: Comparison of the interventions with respect to the HbA1c levels after 1 year

Description of the primary efficacy analysis and population: The primary endpoint will be analysed using ANCOVA for the HbA1c levels, with the baseline value as a covariate and the treatment arm and stratification categories as factors. A closed testing procedure will be used for multiple comparisons. Thus, the three comparisons between the arms will be performed at the nominal significance level of 5% if the global test result is significant. Because the comparison of the surgical groups is of such interest, this comparison will be performed regardless of the result of the global test, though a Bonferroni correction will be used if the global test is not significant.

Secondary endpoint: The comparison of the diabetes remission rates between the surgical arms will make use of a chi-squared-test, and an estimate with 95% confidence interval for the relative probability (“risk”) of remission rates will be provided.

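### At BMI 35 and above, drug-free patients already below 6.5% at baseline can count as 1-year remissions, which overstates the remission rates and attenuates the comparison of the surgical arms

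*Protocol*

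**What the plan says.** **Entry (section 4.1).** At BMI 35 kg/m² or above, type 2 diabetes of any degree qualifies. Below 35 the patient must have "unsatisfactory medical non-insulin treatment (multiple medications, HbA1c" above 6.5%, hypo- or hyperglycaemias), or planned or ongoing insulin. None of the exclusions in section 4.2 removes a drug-free patient with HbA1c below 6.5%.

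**Endpoint.** Section 1.1 gives remission its rank: "The key secondary endpoint for the surgical arms is the diabetes remission rate after 1 year". It then defines it: "Diabetes remission is defined as follows: HbA1c <6.5% without any anti-diabetic medication". The synopsis agrees in substance. Section 2.2 words it differently: "Definition T2DM remission: HbA1c <6.5% without indication for anti-diabetic medication", and section 9.2.2 repeats that wording. Neither version refers to the patient's state at baseline.

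**Analysis (section 9.5.2).** "The comparison of the diabetes remission rates between the surgical arms will make use of a chi-squared-test", with a relative probability of remission and its 95% confidence interval. No baseline restriction or adjustment is stated. For HbA1c, by contrast: "The primary endpoint will be analysed using ANCOVA for the HbA1c levels, with the baseline value as a covariate". Section 9.5.1 makes the per-protocol population the main one and ITT secondary. A patient without remission data is treated as not in remission.

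**Randomisation (section 9.1).** "A randomisation ratio of 1:1 will be used", by minimisation on BMI, "Current insulin treatment" (yes or no) and sex.

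**The concern.** Remission should describe a patient who left the diabetic or drug-treated state after surgery. As fixed here, it also covers a patient who was never in that state during the trial. An example is a diet-treated patient with BMI 38 and HbA1c 6.2% at Visit 1. This patient is eligible, already satisfies the endpoint before the operation, and is counted as a remission if nothing changes.

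The minimisation factors do not isolate such patients, because the no-insulin category mixes them with patients on oral drugs. The baseline covariate that would account for them appears only in the HbA1c model.

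Two things are at stake: the level of the published remission rates, and the size of the contrast between limb lengths. The protocol wants this evidence to support limb-length recommendations in guidelines (section 1.2).

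**Working it through.** **Inputs from the protocol.** 60 analysed per surgical arm and a 5% level (section 9.4), taken as two-sided. Remission of up to 80% is quoted as background, depending on the definition (section 1.2.1). The protocol gives no remission rate by arm, no power for remission, and no share of patients already meeting the definition, so there is no stated remission figure to reproduce.

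**Assumptions.** Remission of 55% and 80% among patients who can remit. A share f of each arm already meets the definition at Visit 1 and still does at 1 year. Values of f = 5, 10 and 15% are shown for range only.

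**Formulas.**
- Observed rate: q = f + (1−f)p, so the excess over p is f(1−p).
- Risk difference: q2 − q1 = (1−f)(p2 − p1).
- Relative risk: q2/q1, which is closer to 1 than p2/p1 for any f above 0.
- Power: Φ[(d − 1.96·SE0)/SE1], where d = q2 − q1, SE0 = √[2q̄(1−q̄)/n], q̄ is the mean of q1 and q2, and SE1 = √[(q1(1−q1) + q2(1−q2))/n].
- Restricted analysis: the same power formula with p1, p2 and n = 60(1−f).

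**One case in full, f = 10%.**
- q1 = 0.10 + 0.90 × 0.55 = 0.595, and q2 = 0.10 + 0.90 × 0.80 = 0.820.
- The excess is 4.5 points in the lower arm (0.10 × 0.45) and 2 points in the higher arm (0.10 × 0.20).
- The difference is 0.225 instead of 0.25, and the relative risk is 0.820/0.595 = 1.38 instead of 0.80/0.55 = 1.45.
- q̄ = 0.7075, SE0 = 0.0831, SE1 = 0.0805.
- Power = Φ[(0.225 − 0.1628)/0.0805] = Φ(0.773) = 78.0%.

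**Range.**

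| f | Rates, all patients (%) | Difference (points) | RR | Power, 60 per arm | Restricted n per arm | Restricted RR | Restricted power |
|---|---|---|---|---|---|---|---|
| 0 | 55.0 / 80.0 | 25.0 | 1.45 | 84.1% | 60 | 1.45 | 84.1% |
| 5% | 57.25 / 81.0 | 23.75 | 1.41 | 81.2% | 57 | 1.45 | 82.2% |
| 10% | 59.5 / 82.0 | 22.5 | 1.38 | 78.0% | 54 | 1.45 | 80.1% |
| 15% | 61.75 / 83.0 | 21.25 | 1.34 | 74.6% | 51 | 1.45 | 77.7% |

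Restriction gains 1.0, 2.1 and 3.1 points of power. At f = 15% the total loss is 84.1 − 74.6 = 9.5 points, so restriction regains about a third. The rest is lost because fewer patients are able to remit.

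**Second assumed pair, 60% versus 80%.** At f = 10% the rates become 64% and 82%, the relative risk falls from 1.33 to 1.28, and power falls from 67.0% to 60.5% (62.4% restricted). At f = 20% the rates are 68% and 84%, the relative risk is 1.24, and power is 53.7% (57.2% restricted). The pattern is the same.

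**The case against.** The strongest objection is that this is not a failure of validity. Patients are randomised 1:1, so those already meeting the definition fall equally into both arms in expectation. A test on 1-year status in all analysed patients answers a legitimate question. That stands. A reader might infer bias towards one operation or a false-positive risk, but the documents support neither. A reader might also think surgery is flattered against medical treatment in this analysis, but section 9.2.2 limits remission to the surgical groups.

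Second, every magnitude rests on assumed inputs. That also stands. The protocol's own planning does not suggest a large f: section 9.4 expects a mean HbA1c fall of 2.9 points after surgery, already allowing for lower initial values. Many entrants near 6.2% would fit badly with that, although the 1.4-point pessimistic scenario leaves more room.

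Third, these patients are not certain successes. They may rise above 6.5% or start drugs by 1 year, and in ITT a missing result counts as no remission. Nor does every operated patient enter the main analysis, which is per-protocol. These points reduce the effect without removing it, because neither population excludes patients who met the definition at Visit 1.

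Fourth, one could leave the denominator to the statistical analysis plan. But the protocol already fixes the definition, the test and the populations, and together these count an unchanged patient as a remission. The objection therefore limits the weight of the point but does not dispose of it.

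**Conclusion.** The point holds as one of overstated rates and attenuation in the key secondary endpoint. The direction is algebraic for any f above 0, provided these patients keep their status to 1 year. The size is unknown, because the protocol supplies neither f nor rates by arm. Under 55% versus 80%, f between 5 and 15% moves the relative risk from 1.45 to between 1.41 and 1.34. If f is near 0 nothing of consequence changes.

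It would be tempting to present the fall in power from 84% to 75% at f = 15% as the cost of the definition. That overstates it, since redefining the analysis set recovers only about 3 of those points. The main gain from the change is a rate and a relative risk that mean what they say. The primary HbA1c analysis is not affected.

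**What to change.** In sections 9.2.2 and 9.5.2, in this order:

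1. Reconcile the two remission definitions, one requiring no antidiabetic medication (synopsis, section 1.1) and the other no indication for it (sections 2.2 and 9.2.2), and use one throughout. Who already meets the definition at baseline depends on this choice.
2. Within the stated per-protocol and ITT populations, restrict the remission comparison to randomised surgical patients who do not already meet that definition at Visit 1. Under the no-medication wording this means baseline HbA1c of 6.5% or more, or on antidiabetic medication. Under the other wording, the medication part has to be replaced by a baseline assessment of indication.
3. Report the patients already meeting the definition separately by arm, and keep the all-patient comparison as a sensitivity analysis.

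The cost is a few sentences. HbA1c and concomitant medication are already recorded at Visit 1, and a restriction on baseline status keeps the randomised comparison intact. Eligibility and the primary analysis do not change. The downside is a slightly smaller denominator and a slightly lower headline remission rate.

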## 1.2 Rationale

### 1.2.1 Hypothesis and Experimental Aspects of the Clinical Trial

T2DM and obesity are major societal burdens that are expected to increase with time. For many patients with known and medically treated T2DM, the HbA1c levels are unsatisfactorily high. Moreover, there are a number of patients suffering from hypo- or hyperglycaemic episodes.

In morbidly obese patients, bariatric surgery is a widely accepted therapy option. So far, gastric bypass is the so called "gold standard". Besides long lasting weight loss, there are well known metabolic benefits.

Bypassing the proximal small intestine and food restriction following RYGB has been shown to improve glucose metabolism dramatically within days, prior to weight loss in obese patients with T2DM. Depending on the definition, remission rates of up to 80% are reported. However, RYGB is a major surgical procedure, related to relevant morbidity and mortality and is irreversible. In a meta-analysis Buchwald et al reported a 30-day mortality after RYGB of 0.5%. [1]

The Roux-en-Y gastric bypass can be considered to be the gold standard for metabolic surgery. However, there is no definition of the optimal limb length in either bariatric or metabolic surgery. Some data favour a longer biliopancreatic limb over a longer alimentary limb. Nergaard et al. showed greater weight loss for the longer biliopancreatic limb and also metabolic improvement; however, the metabolic effects require further studies due to the study design. [9]

The reabsorption of bile acids has an independent positive metabolic effect. Obese patients are known to have lower serum bile acid levels. Following bypass surgery, serum bile acids increase and they are most likely an independent factor for metabolic improvement.

They act on different pathways and influence glucose metabolism, insulin resistance, lipid metabolism, gut hormones, gut microbiota etc. in a beneficial way for the patient. [5-8]

Most likely the mini-bypass functions that way – having a long biliopancreatic limb. However, with a Roux-en-Y reconstruction we do not have the risk of bile reflux into the pouch (and unclear GERD and cancer risk).

In our trial, we intend to investigate the efficacy and safety of the stRYGB and cIIRYGB compared to standard medical treatment in the short and midterm on patients suffering T2DM.

The Bariatric Surgery Section is well prepared for such study; we are currently performing a prospective randomized trial on glucose metabolism with an exercise intervention following bypass surgery (GluMBSE, K74-1). From 2013 we performed little more than 100 bariatric operations per year, mostly RYGB and in January 2014 we became a certified “Competence Center for Bariatric Surgery”.

A number of outpatient endocrinologists / diabeticians have agreed to participate in the study.

Metabolic surgery (surgery mainly for T2DM) is continually gaining acceptance. There are only few data from prospective trials, but all recent reviews/meta-analyses indicate that metabolic surgery is beneficial. However, due to the lack of (long term) data, no conclusive statement is possible and more studies are required. [2] Consequently, in the German guideline for Bariatric Surgery metabolic surgery is recommended for T2DM in patients with a BMI <35 kg/m^2 preferably within studies. [3]

There is a lack of studies investigating the limb length of RYGB with respect to best metabolic changes.

In this prospective randomized trial we want to compare cIIRYGB with the current gold standard stRYGB for metabolic surgery and compare these to standard non-surgical care.

We aim to:

1. Compare the efficacy of medical treatment, cIIRYGB and stRYGB regarding HbA1c change
2. Compare cIIRYGB and stRYGB regarding diabetes remission.
3. Implement limb length recommendations for the RYGB into guidelines.
4. Demonstrate the efficacy of metabolic surgery. As mentioned, several small trials suggest that metabolic surgery is beneficial. So far, metabolic surgery is only recommended when performed within studies. We hope to increase the value of existing data to be implemented in new guidelines.
5. By having a long term follow up at our centre, we hope to collect and analyse important long term data later on.
6. We want to prove that metabolic surgery is beneficial to the patients not only for glycaemic control. Since a sufficient weight loss will be achieved in most patients we expect other obesity associated comorbidities (such as hypertension, GERD, sleep-apnea-syndrome, fatty liver, NASH etc.) to improve.

### 1.3 Risk-Benefit Considerations

The trial will be conducted in accordance with the Guidelines for Good Clinical Practice (GCP). Prior to its start, the trial has to be approved by the Ethical Committee at the University of [REDACTED]

The study will be fully explained to participating patients and inclusion will not be initiated prior to obtained written consent. Patients can withdraw at any point without any disadvantage.

All treatment activities within the study (such as operations (RYGB), endoscopy (routine [REDACTED] prior RYGB), oral or subcutaneous antidiabetic medication) are standard procedures for the population treated and thus covered by the medical insurance.

All follow-up examinations are without any risk and blood samples will only be taken when routine blood will be taken anyway.

Compared to the risk of (poor glycaemic control and) developing diabetes complications, the risks of metabolic surgery are low. However, there are no long term data.

All follow-up examinations are without any risk and blood samples will not be taken for the study alone.

The benefits expected from this trial (better T2DM control, substantial weight loss) clearly outweigh the slight risks.

Participants of the control group will benefit from the much more intensive "Bariatric follow up", what includes an intensive questioning of eating behaviours, extended laboratory investigations (vitamins, trace elements and supplementation if indicated) and investigations such as resting energy expenditure or body fat mass etc..

## 2 OBJECTIVES

### 2.1 Primary Objective

Primary efficacy endpoint:

- HbA1c values after 1 year

### 2.2 Secondary Objectives

Main secondary efficacy endpoint:

- T2DM remission rate after 1 year  
Definition T2DM remission: HbA1c <6.5% without indication for anti-diabetic medication
- Weight loss
- General wellbeing (SF-36 questionnaire, IPAQ) and cognitive function (TMT and MST task)
- Anthropometry (Body weight, BMI, WHR (waist to hip ratio), Body fat mass (BIA))
- Clinical parameters (fasting glucose, fasting insulin, fasting c-peptide, HOMA-IR index, Serum lipids)

Further investigated parameters:

- MRI (liver, subcutaneous and visceral fat mass, brain and spinal cord: inflammation, size general and –grey matter)
- Intima-media-thickness (IMT) A. carotis com.
- Liver volume (MRI), function and morphology
- LiMAx test (functional liver test)
- Indirect calorimetry
- Serum concentration of bile acids, GLP1, PYY, GIP, ghrelin (total and active), obestatin, leptin, leptin BP, adiponectin, chemerin, fetuin-A, Nampt, RBP4, Vaspin, OBBP, betatrophin (presently favored to be examined; extra serum will be frozen and stored for potentially new future parameters)
- Inflammatory markers: CrP, WBC, IL-6, TNF $\alpha$
- Average caloric intake per day

### 3 TRIAL DESIGN AND DESCRIPTION

#### 3.1 Trial Design

Open prospective randomized parallel group trial with an additional observational control arm.

The patients in the two surgical arms will not be informed as to which version of the operation they received until completion of the trial whereas, clearly, the control arm cannot be blinded with regard to treatment. If logistically feasible, study visits will be performed by personnel unaware of which surgical procedure was performed.

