### 6.3 Enrolment in the Trial (Baseline-Visit) and Randomisation

#### Intervention-Groups:

Immediately after the screening (inclusion/exclusion criteria) and agreement to take part in the study, the patient will be discussed at the interdisciplinary “Board for Bariatric Surgery” and in case of a vote for the study inclusion the responsible medical insurance company will be asked to cover the treatment expenses. After a positive answer of the insurance company to cover the expenses for RYGB the baseline examinations will be performed (see flow chart) and the patient’s data will be given to the trial site.

Patients will be randomised by the trial site and the patients will immediately receive information as to which group they belong to by one of trial staff members.

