#### **Randomisation procedure (RYGB)**

If a patient has signed the Informed Consent form and is eligible for the trial the investigator will proceed as follows:

- Assignment of a Patient-ID: In the patient identification list (PIL, see investigator site file), fill in the patient personal data at the first free position of the list. The Patient-ID printed in the list at this position is assigned to the patient and will be used throughout the study as a pseudonym for the patient.
- Login at the randomisation-site, preferably via the MS Internet Explorer. The user will be asked for the Patient-ID, for check of eligibility criteria, presence of informed consent in writing and stratification items. Enter these items and then click the randomisation button. The system will return to you the intervention arm of the patient.

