### 9.2.3 Safety Outcomes

Safety will be assessed by tabulating adverse and serious adverse events. A comparison of complications directly related to the interventions will be provided.

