#### 18.1.3 Determining the Causal Relationship

The investigator must assess whether or not the Adverse Event is causally related to the administration of the trial intervention. The following classification is to be used.

- Reasonable possibility
- No reasonable possibility

A reasonable possibility exists, if one of the following WHO-UMC criteria is met:

- occurring in a plausible time relationship, and which cannot be explained by concurrent disease or other drugs or chemicals
- with a reasonable time sequence, unlikely to be attributed to concurrent disease or other drugs or chemicals
- with a reasonable time sequence, but which could also be explained by concurrent disease or other drugs or chemicals
- more data is essential for a proper assessment
- cannot be judged because information is insufficient or contradictory

No reasonable possibility exists, if the following WHO-UMC criterion is met:

- with a temporal relationship which makes a causal relationship improbable, and in which other drugs, chemicals or underlying disease provide plausible explanations.

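### The investigator is shown the arm and the same role rates relatedness with no masking condition, so the stRYGB versus cllRYGB comparison of related complications may rest partly on unmasked judgement

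*Protocol*

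**What the plan says.** Section 3.1 labels the trial open ("Open prospective randomized parallel group trial with an additional observational control arm") but sets two masking aims within the surgical arms. Patients: "The patients in the two surgical arms will not be informed as to which version of the operation they received until completion of the trial". Staff: "If logistically feasible, study visits will be performed by personnel unaware of which surgical procedure was performed". The second is conditional, and nothing records whether it was met at a given visit.

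Section 6.3, under the randomisation procedure, names who acts: "If a patient has signed the Informed Consent form and is eligible for the trial the investigator will proceed as follows". At the end of those steps, "The system will return to you the intervention arm of the patient". The same section, under the intervention groups, adds that "the patients will immediately receive information as to which group they belong to by one of trial staff members".

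Section 18.1.3 assigns causality: "The investigator must assess whether or not the Adverse Event is causally related to the administration of the trial intervention". It attaches no condition about knowledge of the arm. Section 12.2 dispenses with a safety monitoring board, and the protocol describes no adjudication of events.

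Relatedness then appears in three planned outputs. Section 9.2.3: "A comparison of complications directly related to the interventions will be provided". Section 9.3.2 gives the proportion of procedure-related complications by arm with confidence intervals. The Synopsis gives descriptive statistics by arm for related adverse events. Section 9.2.3 also tabulates all AEs and SAEs without reference to cause.

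**The concern.** The two operations differ only in limb length (5.1), and the protocol records an expectation: section 1.1 anticipates that the changed-limb version will be superior. Section 1.2 hopes to carry limb-length recommendations into guidelines, so the relative complication profile of the two operations matters to how the trial will be used.

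Relatedness is a judgement, and it decides which events enter the related-complication comparison. If the rater knows the limb length, otherwise similar events could be classified differently by arm. A difference could then appear, or a true one be diluted, without any difference in what happened to patients. The operating surgeon cannot be masked. A follow-up rater often could be, and section 3.1 already contemplates such staff. The randomisation step in 6.3 nevertheless gives the arm to a role that need not have it for follow-up, and no later section compensates.

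**Working it through.** **1. Who learns the arm, and when.** Under 6.3 the investigator logs in at Visit 1 and the system displays the arm. Surgery may follow up to 8 weeks later (6.3). Release is not limited to those who will operate.

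**2. What surgical patients learn.** Section 3.1 withholds the version of the operation until the trial is complete. Section 6.3 has a staff member tell patients their group at once. That sentence concerns randomised patients only, and controls are not randomised, so on its natural reading the group is the limb-length arm. The two sections conflict. If 6.3 is followed, patients can also pass the arm on to visit staff who were meant not to know it.

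**3. Who rates.** Section 18.1.3 names the investigator. This is a role. The person who randomises and the person who rates may differ, but nothing requires that, and nothing requires the rater to be unaware of the arm.

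**4. Which outputs depend on the rating.** The related-complication outputs in the Synopsis, 9.2.3 and 9.3.2 do, if relatedness there means the 18.1.3 rating. The protocol does not state this link, but it names no other source. The all-event AE/SAE tabulation in 9.2.3 does not depend on it. Nor does the HbA1c endpoint.

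**5. How much discretion 18.1.3 leaves.** The *Reasonable possibility* category takes in events that concurrent disease could also explain, events needing more data, and events that cannot be judged. *No reasonable possibility* needs both an improbable time relationship and a plausible alternative explanation. Most doubtful events are therefore classed as related by rule in either arm. The remaining judgement is mainly whether the timing is plausible or improbable.

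**6. Size.** The protocol gives no complication rate and no attribution rate, so there is no figure to reproduce. The form of the bias can still be written down. Let p be the true event proportion, equal in both arms, and a₁ and a₂ the probabilities that an event is rated related.

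- Apparent risk ratio = a₁/a₂. Apparent risk difference = p(a₁ − a₂).
- Assumed a₁ = 0.90, a₂ = 0.80: ratio 0.90/0.80 = 1.125. With p from 0.10 to 0.30, the difference is 0.10 × 0.10 = 1 point to 0.30 × 0.10 = 3 points.
- Assumed a₁ = 0.90, a₂ = 0.70: ratio 0.90/0.70 = 1.29. The difference is 0.10 × 0.20 = 2 points to 0.30 × 0.20 = 6 points.

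For scale, with 60 analysed per surgical arm (9.4) and an assumed related rate of 20% in each, the 95% half-width for the difference is 1.96 × √(2 × 0.20 × 0.80 / 60) = 14.3 points. These inputs are assumptions chosen only to show the mechanism. The rule in step 5 pushes both attribution probabilities upward, and as both approach 1 the ratio approaches 1.

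**The case against.** The strongest reply is that this is a declared open trial, that unmasked causality rating is ordinary in surgery, and that the protocol goes further than it must by seeking masked visit staff where it can. Adverse events are collected at those visits (6.4), and showing the arm to one user at randomisation does not unmask everyone else. The question in 18.1.3 is whether an event follows from the intervention, and both arms are a gastric bypass with the same pouch size, so limb length need not enter the answer. The rule in 18.1.3 settles most doubtful cases the same way in both arms. The safety outputs are estimates and tabulations with no stated hypothesis test. Finally, the patient file is the source for clinical data (11.1) and would ordinarily hold the operative details, so hiding the arm on a screen will not mask every rater.

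Most of this stands, and it limits the point. A reader might infer that the randomisation step defeats the masking aim outright, that the safety comparison is invalid, or that ambiguous events would split sharply by arm. The protocol does not support those readings: the investigator is not necessarily one person, the causality rule narrows the discretion, and an all-event tabulation exists. Nor does it support a demand that every rating be masked, since 3.1 itself doubts that the staffing allows this in a single-centre trial.

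What does not fall away is that the protocol sets a masking aim, releases the arm more widely than the aim suggests, contradicts itself on what patients are told, and has no record of who knew the arm when an event was rated.

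**Conclusion.** The point holds in a limited form. The comparison of related complications between stRYGB and cllRYGB may rest partly on ratings made with knowledge of the arm, and the protocol as written would not let a reader tell how often. The effect is probably modest, and no size can be derived from the document. The ratios of 1.125 and 1.29 above are illustrations on assumed inputs and should not be quoted as estimates.

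The conclusion assumes that the related-complication outputs draw on the 18.1.3 rating and that at least some raters know the arm. The statistical analysis plan was not available and may define the outputs more closely, but who sees the arm and who rates events are conduct rules that belong in the protocol. The primary endpoint and the all-event AE/SAE tables are unaffected. The separate conflict between 3.1 and 6.3 on what surgical patients are told is plain on the text and needs reconciling in any case. This is worth correcting, but it does not threaten the trial's main conclusion.

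**What to change.** 1. **Section 6.3.** Release the arm only to the staff who need it for surgery, and give other trial staff a confirmation of randomisation without the arm. Reconcile 3.1 and 6.3 on what surgical patients are told and when.
2. **CRF and section 18.1.** Add a tick-box recording whether the person rating relatedness and intensity knew the arm at the time. Keep masked rating as an aim where feasible, so that no staff are added.
3. **Section 9.2.3.** Present the stRYGB versus cllRYGB comparison with confidence intervals for all AEs and SAEs regardless of relatedness, beside the related-only comparison. Report the share of ratings made with knowledge of the arm.

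The cost is a small change to the randomisation tool, one CRF item and one extra table. Perioperative events, and ratings by staff who have seen the operative notes, will stay unmasked. The tick-box flags these but does not remove them. For patients already randomised, step 1 comes too late, but step 2 still serves their remaining visits and the all-event comparison in step 3 can be made for everyone.
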